DMW has evolved based on the evidence base generated from the Scottish pilot and now incorporates an app to be used with mobile devices, which includes tailored *push* decision support, including health warnings and reminders to patients and clinicians. It is this enhanced version of DMW that, as part of the GM Diabetes My Way project, will be offered to all patients with T2D in GM from August 2019 to March 2022. DMW in GM is a collaborative led by the Greater Manchester and Eastern Cheshire Strategic Clinical Networks. Their aim is to provide a more comprehensive self-management and learning offer than is currently available to people with T2D in GM by delivering an enhanced version of DMW across the region. An additional aim is to improve the uptake of the system across all patient groups.

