**Diabetes My Way–related objectives**
To assess intervention-related changes in hemoglobin A_1c_ (HbA_1c_) levels, systolic blood pressure, cholesterol, smoking, and body weight or BMI (compared with controls and within-person changes).To assess patient uptake (proportion offered intervention who take it up), engagement (time spent on the web and content viewed), user experience (usability, knowledge, and ability to self-manage), retention (proportion of people interacting with the intervention more than once), completion (proportion of people interacting with the intervention who use it within 2 months of the end date (March 31, 2022), and health care use (clinic and hospital attendance and medication use).To assess how Diabetes My Way (DMW) is integrated into care pathways in primary care.

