#### Enrollment and Informed Consent

Enrollment to the DMW intervention will be facilitated through the website, and patients will be directed to the participant information sheet. Providing patients are aged ≥18 years and have a diagnosis of T2D, they will be able to express their interest in taking part in the study by submitting their contact details via the DMW website. Patients will register for web-based services via their general practitioner (GP) who will confirm their identity by checking their documentation. Patients are required to use these web-based service codes to register for DMW and answer a number of inclusion and exclusion criteria. Once registered (and where they match the criteria), the study consent form will be introduced. If and when completed and submitted, the patient’s account is activated, and they are enrolled in the study. When registered, but not matching the study criteria, the patient will be given access to DMW, but not entered into the study or consent process.

Enrollment to other digital interventions will also occur via the DMW website. On the basis of the inclusion and exclusion criteria, participants enrolled and using the DMW intervention will be invited to take part in additional substudies involving an additional digital intervention (Oviva or Changing Health allocated to alternate eligible participants or MyCognition). The above procedure for communicating participant information and obtaining informed consent will be repeated.

We will invite participants to enroll with either Oviva or Changing Health behavioral interventions until 600 have attended each intervention. These interventions will be offered to alternate participants enrolling with DMW, ensuring that the numbers receiving each intervention remain similar.

All DMW participants will be provided with the option of completing the MyCognition web-based cognitive assessment and will be offered the MyCognition intervention until 1000 have completed the intervention. When 1000 people have completed the intervention, DMW participants will continue to be offered the option of completing the MyCognition web-based cognitive assessment but will not be offered the MyCognition intervention. Participants will be invited to complete the MyCognition web-based cognitive assessment every 3 months during the study (a maximum of 3 times). Those completing these assessments, but without receiving the intervention, will act as a control group.

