#### Biochemical Data

All blood sampling (eg, HbA_1c_ and serum lipids) will be conducted via routine clinical care. Participants who did not have a blood sample taken within the preceding 3-6 months will be advised through a message on the DMW website to arrange a diabetes review (weight, blood pressure, smoking status, medication review, HbA_1c_, and lipids) with their practice team at the time of enrollment in line with standard clinical care according to National Institute for Health and Care Excellence (NICE) guidance 28 [36] Participants will be advised to have repeat weight, blood pressure, medication review, and blood tests every 3-6 months in line with standard clinical care according to NICE guidance 28 [36]. Study participants will not be subject to any investigations outside of their routine care unless clinically indicated. Blood test results will be transferred to DMW from the primary care record.

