#### Duration of Data Access

The University of Manchester will request primary care data on study participants for the period April 1, 2016, to March 30, 2022, through DMW This will enable a 3-year assessment of *baseline* levels of risk factors such as HbA_1c_ and blood pressure before study commencement (July 2019), and up to the end of the intervention (March 31, 2022).

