In the presence of time series data, we will use an interrupted time series design for each outcome of interest, which takes into account the preintervention trends of the outcome as well as the information on controls and quantify the effect of the intervention on future outcome levels. If only 2 time points are available (eg, before and after the intervention), we will use a simple linear regression model with clustered errors or a paired 2-tailed *t* test to compare means in each outcome at the 2 time points.

For example, for the main outcome, change in HbA_1c_ levels, we will compare changes from baseline (defined as April 1, 2016, to July 1, 2019) during the intervention period (July 1, 2019, to March 31, 2022) in matched participants and controls after adjusting for clinically significant differences in baseline weight, blood pressure, cholesterol, creatinine, cardiovascular disease, and smoking.

If the numbers of cases and controls are large, we will explore effect heterogeneity in subgroup analyses (as separate models or using interaction terms in the main models described above) by ethnicity, age groups, socioeconomic deprivation quintile, cognitive function (assessed by MyCognition), and level of engagement with digital interventions.

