## Results

As of May 10, 2021, a total of 316 participants have been recruited for the quantitative study and have successfully enrolled. A total of 278 participants attempted to register but did not have appropriate permissions set by the GPs to gain access to their data. A total of 10 participants have been recruited for the qualitative study (7 practitioners and 3 patients). An extension to recruitment has been granted for the quantitative element of the research, and analysis should be complete by June 2022. Recruitment and analysis for the qualitative study should be complete by June 2021.

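### The main HbA1c comparison splits time at July 1, 2019 for everyone, although each participant starts the intervention on an individual, later date

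*Protocol article*

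**What the plan says.** In the Analysis section of the quantitative study (Overview), the main outcome is worked through, for participants and their matched controls, as a comparison of "changes from baseline (defined as April 1, 2016, to July 1, 2019) during the intervention period (July 1, 2019, to March 31, 2022". Duration of Data Access repeats the split: baseline is the time "before study commencement (July 2019), and up to the end of the intervention (March 31, 2022".

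Other sections describe a different exposure pattern:
- Background says that the enhanced DMW "will be offered to all patients with T2D in GM from August 2019 to March 2022".
- Enrollment and Informed Consent makes the start individual, at submission of the consent form: "If and when completed and submitted, the patient’s account is activated, and they are enrolled in the study". Oviva, Changing Health and MyCognition are entered from within DMW, so no earlier than DMW itself.
- Results reports: "As of May 10, 2021, a total of 316 participants have been recruited for the quantitative study and have successfully enrolled". It adds that recruitment has been extended.
- Biochemical Data says: "Participants who did not have a blood sample taken within the preceding 3-6 months will be advised through a message on the DMW website". The message advises them to arrange a diabetes review, HbA1c included, at enrolment.

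No section of the article sets an individual index date for participants or assigns one to controls.

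**The concern.** A before-and-after contrast needs the dividing line to fall where exposure begins. Here it falls on a date when nobody could be exposed, and for many participants it falls long before enrolment.

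Three things follow:
- HbA1c values taken after July 1, 2019 but before enrolment are classed as intervention-period data.
- The test prompted at enrolment, which is the natural baseline, is classed the same way.
- For someone enrolling late, the newest admissible baseline value may be nearly two years old or more.

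The rule governs the primary HbA1c comparison for DMW, Oviva and Changing Health. It also sits badly with the article's own wording elsewhere: the sample size section defines the outcome as HbA1c once the intervention has been received, and the Analysis section speaks of pre- and post-intervention comparisons.

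**Working it through.** **Inputs.** From Sample Size Calculations: SD 15 mmol/mol, difference 5 mmol/mol, 5% significance level (taken as two-sided), 86 participants and 430 controls, 80% power, 90% providing data. From Analysis: window July 1, 2019 to March 31, 2022. From Background: earliest start August 2019. From Results: 316 enrolled by May 10, 2021.

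**Step 1: the plan's own figure.** With k controls per participant, n = (1 + 1/k) × [SD × (1.960 + 0.842) / difference]². At k = 5 this gives 84.8, so 85 participants and 425 controls, close to the stated 86 and 430. The standard error at 86/430 is 15 × √(1/86 + 1/430) = 1.772. Then 5/1.772 − 1.960 = 0.862, which is 80.6% power. Also 86/0.9 = 95.6, so 96. The figure reproduces at 1:5. The text states 1:10, which is a separate matter.

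**Step 2: how much of the window is unexposed.** The window is 1,004 days (about 33 months). August 1, 2019 is day 31 and May 10, 2021 is day 679. With uniform enrolment, the mean unexposed share f is the midpoint of the enrolment period divided by 1,004:
- enrolment to May 10, 2021: (31 + 679)/2 = 355; 355/1,004 = 35.4%
- enrolment to March 31, 2022: (31 + 1,004)/2 = 517.5; 517.5/1,004 = 51.5%

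For a person enrolled on May 10, 2021, 679/1,004 = 67.6% of the window precedes enrolment, and the newest admissible baseline value is 679 days old.

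**Step 3: illustration of dilution.** Assumptions that the article does not state: HbA1c tests spread evenly over the window, all in-window values averaged, full effect from enrolment, no other difference between groups, SD kept at 15. The apparent effect is then 5 × (1 − f), and power is Φ(apparent effect/SE − 1.960). The last column uses 316 × 0.9 = 284 DMW participants with five controls each (1,420), SE = 15 × √(1/284 + 1/1,420) = 0.975.

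| Enrolment assumed | f | Apparent effect (mmol/mol) | Power, 86/430 | Power, 284/1,420 |
|---|---|---|---|---|
| All on August 1, 2019 | 3.1% | 4.85 | 78% | above 99% |
| Uniform to May 10, 2021 | 35.4% | 3.23 | 45% | 91% |
| Uniform to March 31, 2022 | 51.5% | 2.42 | 28% | 70% |

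At 86/430, other values of f give 72% (f = 10%), 62% (20%), 51% (30%) and 29% (50%).

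**Step 4: the alternative summary.** If only the last value before March 31, 2022 is used, most people contribute an exposed value. Dilution is then small, except for late enrollees and those whose last test came before enrolment. The outdated baseline remains in either case.

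**The case against.** The strongest reply is that the dates come in a sentence offered as an example, and that the size of any harm rests on a summary rule that the article does not contain. The second half stands: averaging is an assumption, and so is the enrolment pattern. Enrolment running uniformly to March 2022 is close to the worst case, because that is when the offer ends and no recruitment end date is given. Averaging repeated values would also lower the SD below 15. The first half does not rescue the rule. The example concerns the main outcome, it is the only window definition given, and Duration of Data Access repeats the split.

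A reader might infer more than the documents support:
- *That the primary contrast has only about 28% power.* That needs averaging, near-worst-case enrolment and the 86-participant minimum for one intervention. DMW had already enrolled 316.
- *That the bias is certainly toward no effect.* Mixing unexposed time dilutes a true effect. But under Comparison Group the controls are people who declined the offer, and their pre-enrolment course may differ in either direction.
- *That the interrupted time series breaks at July 2019.* The text gives no break date for it.
- *That the enrolment date is missing from the linked data.* The list of items sent to NHS Digital is introduced as non-exhaustive, and DMW also supplies data to the university.
- *That the pandemic confounds the primary contrast through this split.* Controls share the same calendar windows, so change common to both groups cancels. The within-person comparison, which is secondary, is the exposed one.

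**Conclusion.** The calendar split is wrong as written. It is a stated rule for the primary outcome, not a detail left to an analysis plan, and it contradicts the rolling, individual start of exposure described in the same article. It is certain that unexposed HbA1c values between July 1, 2019 and enrolment are counted as intervention-period data, and that late enrollees get an outdated baseline.

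The size is not certain. Under averaging, uniform enrolment and a constant SD of 15, a true 5 mmol/mol appears as about 3.2 to 2.4. Power falls from about 80% to between 45% and 28% at 86/430, but would be about 91% to 70% with 284 DMW participants and 1:5 controls. Under a last-value rule the dilution is small for most participants. These are illustrations, not estimates for this study. The point should be corrected before analysis because it affects the main estimates for DMW, Oviva and Changing Health and is cheap to repair.

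**What to change.** Replace the calendar split in Analysis and in Duration of Data Access with an individual index date:
- **Participants:** date of account activation for DMW, and a separate start date for each adjunct intervention.
- **Controls:** the index date of the participant to whom they are matched. They must be eligible non-users on that date.
- **Baseline and outcome:** baseline is HbA1c before the index date. The outcome is HbA1c in a prespecified window after it, identical in both groups, with a stated rule for several values.
- **Time series:** place any interruption at the index date.
- **Data:** confirm that the activation date is available in the linked data.

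The cost is revised wording, one date field, and the loss of the latest enrollees who have no follow-up after their index date.

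A separate, secondary point that applies to DMW only: Textbox 1 defines "completion (proportion of people interacting with the intervention who use it within 2 months of the end date (March 31, 2022". A first login in March 2022 therefore counts as completion, while a long-term user who stopped in December 2021 does not. Define DMW completion by time since enrolment. Completion for Oviva and Changing Health is course completion and is not affected.

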### Quantitative Study

#### Design

DMW, behavioral interventions (Oviva and Changing Health) and MyCognition will be prospective controlled cohort studies. Intervention-related changes in outcomes such as glucose levels will be assessed after adjusting for prospective changes observed in matched cohorts of patients not receiving any intervention.

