#### Comparison Group

Within the short time frame available for the study, a randomized controlled trial will not be possible; therefore, the effectiveness of the interventions will be compared with groups of people choosing not to take up the offer of interventions. Data on this comparison group will be sourced from NHS Digital as part of the national GP Data for Planning and Research program. The comparison group will be sourced from patients registered in GM, the other inclusion and exclusion criteria being applied. Controls (not using the intervention) will be matched (up to 10:1) with study participants on age (+2 or −2 years), gender, ethnicity, and general practice. When appropriate, we will increase the number of controls per participant to enable additional matching on baseline levels of outcome measures, such as HbA_1c_ levels. Where there are clinically important differences between participants and controls in relation to other characteristics such as prevalent cardiovascular disease, we will include these variables as covariates regression models.

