**Diabetes My Way, Oviva, and Changing Health behavioral interventions**
Primary outcomeChange in hemoglobin A_1c_ levels [26,27].Secondary outcomesChanges in body weight or BMI, blood pressure, cholesterol, and smoking [28].Uptake, engagement, user experience, retention, completion [29], and health care use (clinic and hospital attendance and medication use).Impact of primary care staff on knowledge, skills, and confidence in diabetes management [30].Modifying effect of cognitive function [31].

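### Heterogeneity by cognitive function and engagement cannot be estimated against controls who have neither measure; report both as associations within participants

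*Protocol article*

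**What the plan says.** Under Analysis, Overview, the protocol article states "If the numbers of cases and controls are large, we will explore effect heterogeneity in subgroup analyses", to be fitted "as separate models or using interaction terms in the main models described above". The listed modifiers are ethnicity, age group, deprivation quintile and then "cognitive function (assessed by MyCognition), and level of engagement with digital interventions". Textbox 3 separately lists "Modifying effect of cognitive function" as a secondary outcome for DMW, Oviva and Changing Health, without the condition on numbers.

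Under Quantitative Study, Design, outcomes are adjusted for changes in "matched cohorts of patients not receiving any intervention". Under Comparison Group, the interventions are "compared with groups of people choosing not to take up the offer of interventions", and "Data on this comparison group will be sourced from NHS Digital". The item lists for these controls (the Diabetes My Way data section and the section on NHS Digital data) contain demographic, clinical and service-use items. They contain no cognition score and no usage metric.

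Cognition is measured inside the platform: "All DMW participants will be provided with the option of completing the MyCognition web-based cognitive assessment" (Enrollment and Informed Consent). Engagement is app or website use, such as visits and time spent (Analysis, Overview; User Engagement With Digital Intervention).

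**The concern.** To ask whether a factor modifies a treatment effect, one must know how the outcome varies with that factor among the untreated as well as the treated. Here the factor is recorded only in users. A difference in HbA1c change between high-cognition and low-cognition users, or between heavy and light users, then has two possible sources: the intervention works better in one group, or that group would have done better anyway. The planned comparison cannot tell them apart.

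Engagement is the harder case. It arises after enrolment, the user chooses it, it may itself depend on how the patient is faring, and for a non-user it does not exist. At stake is whether an exploratory result is reported as effect modification, or read as dose-response, when it may be prognosis or self-selection.

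**Working it through.** **The plan's own figure.** The only sample size stated for HbA1c concerns the main effect: 86 participants and 430 controls, SD 15 mmol/mol, difference 5 mmol/mol, 5% significance (taken as two-sided), 80% power. With five controls per participant, n = (1.96 + 0.842)² × 15² × (1 + 1/5) / 5² = 84.8, so 85. With 86 and 430 the power is 80.6%, and 86/0.9 gives the stated 96. (These figures correspond to 1:5, although the text says 1:10; nothing below depends on that.) No figure is given for effect modification.

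**Interaction model.** Let T = 1 for participants and 0 for controls, and let M be the modifier. The model needs four columns: 1, T, M and T×M. M is unrecorded in every control. If it is set to any constant there, such as 0, the M column equals the T×M column. A check with 86 participants and 430 controls gives rank 3 for 4 columns. The interaction cannot be separated from M's own association with the outcome.

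**Separate models.** These can be fitted: take participants in one stratum of M with their matched controls, and repeat for the other stratum. The controls are matched on age, gender, ethnicity and general practice (with baseline outcome level where appropriate), not on M. The difference between the two stratum contrasts is therefore

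(true difference in effect) + (difference in HbA1c change between the strata that would occur without the intervention).

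The second term is zero only if M does not predict HbA1c change apart from treatment.

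**Illustration of the second term.** Inputs: SD of HbA1c 15 mmol/mol (Sample Size Calculations); correlation between baseline and follow-up 0.7 (assumed); correlation ρ between M and HbA1c change, regardless of treatment, 0.1 to 0.3 (assumed); M normal and split at its median.

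- SD of change = 15 × √(2 × (1 − 0.7)) = 11.6 mmol/mol.
- Difference in mean M between the halves = 2 × 0.798 = 1.596 SD.
- Spurious heterogeneity = 1.596 × ρ × 11.6 = 1.9, 3.7 and 5.6 mmol/mol for ρ = 0.1, 0.2 and 0.3.

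**Simulation under different assumptions.** The true effect is constant at −5 mmol/mol, SD of change is 15, there are five controls per participant and 2,000 replicates, and M shifts HbA1c change by g mmol/mol per SD whatever the treatment.

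| g | Spurious heterogeneity (mmol/mol) | False-positive rate, 86 participants | False-positive rate, 288 participants |
|---|---|---|---|
| 1 | about 1.6 | 8% | 14% |
| 2 | about 3.2 | 15% | 39% |
| 3 | about 4.8 | 28% | 71% |

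When M is also measured in the controls, the bias is about 0 and the false-positive rate 4 to 6%. More participants leave the bias unchanged and make a false finding more likely.

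**The case against.** The strongest reply is that the plan can be read differently. The Analysis section also provides for pre-post comparisons in participants only, and both Aims and Objectives and the Outcomes overview define secondary outcomes as within-person changes. On that reading the Textbox 3 item needs no control values. This stands as far as it goes: it would be wrong to infer that the Textbox item must mean a comparison with usual care. The subgroup sentence, however, is conditional on the numbers of both cases and controls and refers to the main models, which include the matched comparison. A within-participant analysis would also show association with change, not modification of effect.

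Other points:

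- *The analyses are exploratory and need large numbers.* True, but numbers do not supply the missing variable. Nor can a statistical analysis plan, unless the controls' data change.
- *Some controls do have cognition scores.* In the MyCognition evaluation, DMW users who are assessed without receiving that intervention act as controls. A reader should not infer that no control anywhere has a score. These people use DMW, so they are not untreated controls for it.
- *An interrupted time series with about three years of baseline data removes earlier differences.* Where it can be fitted it deals with pre-existing level and trend, but not with divergence after enrolment.
- *The wider conclusions are at risk.* A reader might infer that the statements on equity and rollout depend on these subgroups. They do not: the Discussion ties equity to the acceptability work and rollout to the main effects.

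**Conclusion.** The point holds for DMW, Oviva and Changing Health. Wherever cognitive function or engagement enters the participant-versus-control models, the interaction is not identified, and stratum-specific contrasts mix treatment heterogeneity with the modifier's own relation to HbA1c change. That part follows from the protocol's definition of the controls and their data, and needs no assumption.

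The size does need assumptions. The range of 1.9 to 5.6 mmol/mol rests on a pre-post correlation of 0.7 and a modifier correlation of 0.1 to 0.3, neither of which the document gives. It should be read only as showing that the error could be comparable with the 5 mmol/mol difference the study is sized to detect. It would go too far to say that false heterogeneity will certainly appear: it arises only if the modifier predicts HbA1c change apart from treatment.

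Heterogeneity by age, ethnicity and deprivation is not affected by this point.

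**What to change.** 1. In Analysis, Overview, remove cognitive function and engagement from the participant-versus-control heterogeneity models. Keep age group, ethnicity and deprivation quintile.
2. Report both as exploratory within-participant associations with HbA1c change, adjusted for baseline HbA1c. Use the baseline cognition score, and engagement from a fixed early window that closes before the outcome is measured.
3. Reword the Textbox 3 item on cognitive function as an association within participants, not effect modification against usual care.

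The cost is a change of wording and a narrower claim: the study would no longer say for whom the interventions work better than usual care on these two factors. Self-selection would still affect the engagement association, so it should be described as such.

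A comparison of Oviva with Changing Health by baseline cognition may be added, since the two are offered to alternate participants and all are DMW users to whom the assessment is available. It addresses only the relative effect of two active programmes and cannot replace the Textbox 3 item. Its power is low: with 86 evaluable per programme, SD 15 and a median split, the interaction has standard error 2 × 15 × √(2/86) = 4.57. For a 5 mmol/mol interaction, 5/4.57 − 1.96 = −0.87, which is about 19% power.
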